### Experimental Plan

This is a French comparative multicentric phase III randomized controlled open trial comparing two groups receiving either somatostatin vs. octreotide of patients undergoing PD or DP with or without splenectomy. The study is controlled against octreotide, the gold-standard treatment for the prevention of postoperative PF. The research methodology is deliberately based on the SOM230 previous publication in the NEJM14, to be able to compare the different results [(13) #1171]. In the experimental regimen group, all patients will receive continuous intravenous infusion of somatostatin-14, 6 mg per day during 6.5 days starting just after skin incision and surgical exploration. In the conventional therapeutic strategy group, all patients will receive conventional prophylaxis arm: subcutaneous octreotide 100 μg 3 times a day for 6.5 days starting just after skin incision and surgical exploration (Figure 2). Amylase will be dosed on postoperative days 1, 3, 5, and 7, in the morning on the 24 h drain fluid and blood. Dosage of α-amylase is obtained with enzymatic colorimetric test, coloration intensity being proportional to the α-amylase activity. It is determined by measure of absorbance increase.

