**Figure 2 F2:**
[figure not shown]
Experimental plan of PreFiPS study.

Patients with newly diagnosed pancreatic disease undergoing pancreatic surgery are screened for inclusion at the first surgical consultation. All patients fulfilling the inclusion criteria are asked to participate in the study. They are included in the study and sign the informed consent the day before surgery. Patients are 1:1 randomized in two arms, in the operating room just after skin incision and surgical exploration to exclude patients with carcinomatosis and metastasis. Surgical procedure is done according to each attending surgeon's preferences. Patients are seen in clinics 1 month after discharge and at 90 postoperative days. Table 3 resumes the chronology of the research.

**Table 3 T3:** Summary the chronology of the research.

**Actions**	**Inclusion visit**	**Surgery**	**Treatment**	**Postoperative days**	**Follow-up visit**	**End of research**
	**(D-1 month)**	**(D)**	**(during 6.5 days after surgery)(^a^)**	**1, 3, 5, 7**	**(D45 ± 7 days)**	**(D90 ± 10 days)**
Informed consent	(A day before surgery)					
History	X					
Clinical examination	X			X	X	X
Para-clinical examination	X				X	X
Amylase dosage in drain				X		
Tests (biochemistry, hematology, etc.)	X			X	X	X
Randomization		X				
Dispensation of treatment			X			
Compliance				X		
Adverse events				X	X	X
Postoperative quality recovery scale only in patients undergoing pancreaticoduodenectomy	(A day before surgery)			Only POD^b^7		

a *Glycemic controls will be done during treatment. Glycemic controls are routine care in patients candidate for pancreatic surgery*.

b *POD, postoperative day*.

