### Randomization

Patients are 1:1 randomized in two groups, in the operating room just after skin incision and surgical exploration to exclude patients with carcinomatosis and metastasis, using permutated blocks of random size to stratify group assignment according to the type of procedure (PD or DP) and the presence or absence of main pancreatic duct dilatation (defined as main-duct diameter of >4 mm at the site of pancreatic transection on preoperative imaging). The randomization list is established centrally by the statistician of the URC et CIC Paris Descartes Necker Cochin before the start of the trial. The document describing the randomization specifications and the randomization list are kept confidentially in a secured place URC et CIC Paris Descartes Necker Cochin. The randomization list is implemented in a randomization tool of the e-CRF on Cleanweb software by the URC et CIC Paris Descartes Necker Cochin. Only the statistician and the person implementing the list in the e-CRF have access to the list during the trial. Randomization is performed by the site staff using the centralized tool in the e-CRF just after skin incision and surgical exploration to exclude patients with carcinomatosis and metastasis.

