### Assessment of Efficacy

The primary efficacy endpoint is a decrease 90 days grade B or C postoperative PF as defined by the last ISGPF classification between patients who receive perioperative somatostatin and octreotide. The definitions of the grade B or C postoperative PF to be used in this study are provided previously. Clinical examination is performed every day to collect manifestations related to PF and its complications. Clinical examination includes temperature, sign of sepsis or infection, and drainage output. Biological evaluation, i.e., amylase dose at 6:00 a.m. on the 24 h drain fluid and blood, is performed on postoperative days 1, 3, 5, and 7 to collect manifestations related to PF. Imaging requested by the clinical manifestation is recorded. Need for reoperation, radiological drainage, and readmission are recorded. Assessment for pancreatic and non-pancreatic complications is made at the time of discharge and in follow-up by the attending surgeon. Pancreatic complications are defined as PF, leak, and abscess. These three complications are typically grouped together because their definitions overlap, the mechanism by which they occur is presumed to be similar (leakage of pancreatic exocrine secretion and/or enteric contents), the presentation is similar (elevated drain output if drain in place or fever/elevated white blood count if no drain in place), and the treatment is the same (percutaneous or operative drainage). When a pancreatic complication has been identified, study drug (somatostatin) or control treatment (octreotide) will be continued until postoperative day 7 and then discontinued. Management of PF is left at each attending surgeon's discretion.

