Multivariate linear regressions will be then performed to adjust these analyses on the stratification variables (data transformation could be done in case of non-normal distribution). Additional analyses could be provided according to different subgroups, i.e., based on the stratification variables (i.e., the type of procedure and the presence or absence of main pancreatic duct dilatation) or on the placement or non-placement of a drain at the time of surgery. In addition, sensitivity analyses could be provided to explore different hypothesis regarding the handling of lost to follow-up patients.

A cost-effectiveness analysis will be performed as a secondary endpoint. The aim of the economic evaluation is to assess the cost-effectiveness of continuous intravenous infusion of somatostatin vs. subcutaneous octreotide in patients undergoing either pancreaticoduodenectomy or distal pancreatectomy. Our methodology follows the French and CHEERS guidelines [(15) #1172]. Effectiveness values will be derived from the clinical endpoints. We propose to use two effectiveness endpoints based on the trial's objectives:

The percent of patients with grade B or C postoperative pancreatic fistula at 90 days.90-day severe complication rate (grade 3–5) and mortality.

We will compute and incremental cost per adverse outcome averted and an incremental cost per survivor. Baseline results will be presented as mean ± SD, median interquartile ranges (IQR), or as frequencies with percentages. Resource use data will be presented as means with standard error of the mean despite non-normal distribution because they better represent per patient data than median values and compared using non-parametric testing. Costs, life-years, and complications will be presented as means with 2.5–97.5% bootstrapped intervals. Between-group comparisons of costs will be performed using the bootstrap *t*-test. Between-group comparisons of effects will be performed using non-parametric testing.

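### The optional drain / no-drain subgroup is defined by a choice made after randomization in an open trial, so its within-subgroup treatment comparisons are open to bias

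*Protocol article*

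**What the plan says.** The protocol article, under Statistical Analysis, introduces subgroup work as optional: "Additional analyses could be provided according to different subgroups". It names the type of procedure and main-duct dilatation as possible subgroup factors, and then adds "or on the placement or non-placement of a drain at the time of surgery". No distinction is drawn between the three.

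Other sections fix when each variable is determined:

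- **Randomization.** The two stratification factors are set before allocation; the list is built to "stratify group assignment according to the type of procedure (PD or DP) and the presence or absence of main pancreatic duct dilatation". Duct dilatation is read from preoperative imaging. Drain placement is not a factor.
- **Randomization, on timing.** "Randomization is performed by the site staff using the centralized tool in the e-CRF just after skin incision and surgical exploration".
- **Experimental Plan, on treatment.** The somatostatin infusion is given at "6 mg per day during 6.5 days starting just after skin incision and surgical exploration". Subcutaneous octreotide starts at the same point.
- **Experimental Plan, on masking.** "This is a French comparative multicentric phase III randomized controlled open trial".
- **Experimental Plan, text after Figure 2.** "Surgical procedure is done according to each attending surgeon's preferences".

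**The concern.** A subgroup analysis by arm is a randomized comparison only if subgroup membership is fixed before allocation, or cannot be influenced by it. Procedure type and duct dilatation meet that condition through the stratification. Actual drain placement does not. It is settled later in the same operation, when the surgeon can know whether the patient is receiving an infusion or injections.

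If knowing the arm changes who receives a drain, drained somatostatin patients need not resemble drained octreotide patients in fistula risk, and likewise for the undrained. A difference, or an apparent interaction, could then arise without any treatment effect, and the trial data could not separate the two explanations. Because the plan lists drain status beside two valid factors without a caveat, a reader of the results would probably give all three the same weight.

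**Working it through.** **The plan's own figures.** For 30% vs 20%, two-sided 5%, 80% power, with pooled variance under the null:

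n = [1.96·√(2·0.25·0.75) + 0.8416·√(0.30·0.70 + 0.20·0.80)]² / 0.10² = (1.200 + 0.512)² / 0.01 ≈ 293.2, rounded up to 294 per arm.

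Then 2 × 294 = 588, and 588 / 0.90 = 653.3, giving 654. Both stated figures reproduce. They do not bear on this point, except that 654 / 2 = 327 per arm is used below.

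**Order of events.** (1) Incision and exploration. (2) Randomization by site staff. (3) Start of the allocated drug, without blinding. (4) The remainder of the operation, at the surgeon's preference. Drain placement belongs to step 4. That the surgeon chooses the drain while able to know the arm is a strong inference from these sections; the article does not say so in those words.

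**How a spurious difference arises.** Split patients into risk classes k with share w_k and fistula rate r_k, the same in both arms (no treatment effect). Let d_k be the probability of a drain in class k. Within one arm:

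- rate among drained = Σ w_k d_k r_k / Σ w_k d_k
- rate among undrained = Σ w_k (1 − d_k) r_k / Σ w_k (1 − d_k)

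If every d_k is equal in the two arms, both rates are equal and the difference is exactly zero. If the d_k differ by arm, the rates generally differ.

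**Moderate to strong scenarios.** Only the 30% overall rate comes from the article (Sample Size Considerations); the rest is assumed. Half the patients are high risk (45%) and half low risk (15%), so the overall rate is 30%. In the octreotide arm, 95% of high-risk and 75% of low-risk patients are drained:

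- drained: (0.5·0.95·0.45 + 0.5·0.75·0.15) / 0.85 = 0.270 / 0.85 = 31.8%
- undrained: (0.5·0.05·0.45 + 0.5·0.25·0.15) / 0.15 = 0.030 / 0.15 = 20.0%

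The somatostatin arm varies as below. Type I error is from 20,000 simulated trials with 327 per arm, each subgroup tested at two-sided 5%.

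| Somatostatin drain use (high / low risk) | Drained rate | Undrained rate | Spurious difference, drained / undrained (points) | Type I error, drained / undrained |
|---|---|---|---|---|
| 95% / 75% (same as octreotide) | 31.8% | 20.0% | 0.0 / 0.0 | 4.7% / 5.2% |
| 95% / 65% | 32.8% | 18.8% | +1.0 / −1.2 | 5.7% / 5.7% |
| 85% / 65% | 0.240/0.75 = 32.0% | 0.060/0.25 = 24.0% | +0.2 / +4.0 | 5.3% / 7.9% |
| 95% / 40% | 0.24375/0.675 = 36.1% | 0.05625/0.325 = 17.3% | +4.3 / −2.7 | 17.8% / 6.9% |

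Differences are somatostatin minus octreotide. In the second and fourth rows the two subgroups move in opposite directions, which would look like an interaction.

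**Extreme illustration.** Shares of 30% low risk (10% fistula), 20% medium (30%) and 50% high (42%) give 0.03 + 0.06 + 0.21 = 30% in both arms. Suppose octreotide surgeons omit drains in all low-risk patients, and somatostatin surgeons in all low- and medium-risk patients:

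- drained: somatostatin 42.0%; octreotide (0.06 + 0.21) / 0.70 = 38.6%
- undrained: somatostatin (0.03 + 0.06) / 0.50 = 18%; octreotide 10%

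Somatostatin looks worse in both subgroups although the overall rates are identical. This case makes drain choice a deterministic function of risk and moves a whole class by arm, leaving 50% vs 30% undrained.

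**The case against.** The strongest reply is that timing alone creates no bias. Drain placement must also depend on the arm, and nothing in the article says that it does. Leaving technique to the surgeon is equally compatible with a fixed personal drain policy applied to both arms. This stands. A reader might infer that the drain-subgroup comparisons are biased; the documents support only that they are open to bias.

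A second reply is that the analysis is optional, is not among the stated objectives, and leaves the primary comparison alone. This also stands and limits the consequence. It does not make the variable a sound one: if the analysis is reported, it will be read beside the stratum subgroups. Nor is this detail awaiting the SAP, because the article itself names the variable. How the subgroup is modelled or tested can properly be left to the SAP.

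A third reply concerns size. The Discussion says drains are widely used in France, without giving a rate, and drain-fluid amylase is scheduled with no exception for undrained patients. The undrained group may therefore be small, and 50% vs 30% undrained is not an expected pattern. This stands; the extreme figures show the mechanism only.

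A reader might also argue that drain status decides whether drain amylase can be measured, so detection is uneven. Within a subgroup that limitation applies to both arms alike. It may explain different fistula rates between drained and undrained patients, but it does not by itself bias the arm comparison inside either group.

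**Conclusion.** The point holds as a minor to moderate weakness in an optional analysis. Actual drain placement is a post-randomization variable in an open trial, and the plan lists it as a subgroup factor on the same footing as two baseline strata. No other section repairs this.

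The spurious difference is zero if drain choice ignores the arm. Under the assumed moderate to strong dependence it is about 0 to 4 points in absolute size, with subgroup type I error of about 5% to 18%. In the extreme illustration it reaches 3.4 points (42.0 − 38.6) among drained and 8 points (18 − 10) among undrained patients. All these sizes rest on risk shares and drain rates that the documents do not give; none is a forecast. The primary intention-to-treat analysis and the subgroups on procedure type and duct dilatation are not affected.

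**What to change.** Remove actual drain placement from the list of treatment-effect subgroups and report drain use by arm descriptively. This changes wording only. Similar drain rates in the two arms should not be read as proof that selection was the same, since equal totals can hide different choices by risk.

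If a drain subgroup is wanted, add one e-CRF field, 'drain planned: yes/no', that must be completed before the allocation is released, and define the subgroup on it. The randomization tool already sits in the e-CRF, so the field can be made a condition of release. It records intent only and leaves the operative decision untouched.

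The cost is one field and a wording change. The downside is that patients already randomized lack the field and cannot contribute to that subgroup. If recruitment is well advanced, dropping the subgroup is the simpler choice.

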## Discussion

Mortality rates after pancreatectomy have decreased to ~2–4% at high-volume centers; however, morbidity after those pancreatic surgeries has remained over the last 30 years between 30 and 50% (16–19). The postoperative morbidity is mainly explained by pancreatic fistula, hemorrhage, and delayed gastric emptying. PF, leak, and abscess area group of complications related to the anastomosis (PD) or closure (DP) of the pancreatic remnant. Pancreatic complications are known to be secondary to the leakage of pancreatic exocrine secretions and/or enteric contents and have been reported in 20–50% of patients who undergo pancreatic resection (1–5). Previous studies have investigated patients and tumor factors associated with the risk of developing postoperative pancreatic fistula, leak, and abscess (1, 20–23). The factor most frequently associated with a decreased risk of these complications is the presence of a dilated pancreatic duct. In addition, tumor location (head/neck vs. body/tail) and the type of resection (pancreaticoduodenectomy vs. distal pancreatectomy) has been reported to be associated with the frequency and severity of pancreatic fistula, leak, and abscess (24). As pancreatic duct size and tumor location cannot be modified, many investigators have evaluated operative and postoperative techniques for reducing the prevalence of postoperative fistula, leak, and abscess after pancreatectomy (25).

Several prospective randomized studies have found pancreaticogastrostomy to be equivalent or only minimally superior to pancreaticojejunostomy with respect to the occurrence of postoperative fistula and leak, and both appear superior to pancreatic duct obliteration without anastomosis (26–28). External drainage of pancreatic duct with a stent seems to reduce leakage rate of pancreaticojejunostomy after pancreaticoduodenectomy, but remain infrequently used (4, 29) and is useless after distal pancreatectomy. In patients undergoing distal pancreatectomy, a variety of techniques for remnant closure have been reported (hand-sewn, stapled, stapled with pledget reinforcement) without clear advantage for any specific technique (30).

The routine use of postoperative drains remains controversial in either the reduction or treatment of pancreatic complications (31, 32), and drains remains widely used in France. Because pancreatic exocrine secretion has been proposed as the mechanism by which pancreatic complications occur, the inhibition of this secretion has been evaluated as a method to reduce the risk of pancreatic complications. Several prospective studies have been performed to assess the utility of perioperative octreotide to decrease pancreatic fistula and leak. The results of all those international and European studies reported a decreased pancreatic fistula/leak rate in patients who received perioperative octreotide. However, there is no worldwide consensus regarding the use of prophylactic octreotide in patients undergoing pancreatectomy. Several reviews and meta-analyses have been performed and conflicting conclusions have been made (12, 33, 34). Criticisms of previous studies have included the lack of stratification for pancreatic duct size and procedure not administering octreotide in the immediate preoperative period. Published meta-analyses have recommended additional randomized studies. Nevertheless, Allen et al. recently published a randomized, double-blind, placebo-controlled phase III trial comparing SOM230 (pasireotide commercially available in France as Signifor) vs. placebo (13) in patients undergoing PD/DP. Interestingly, testing this new somatostatin analog, associated with a stronger affinity for four of five subtypes of somatostatin receptor, the authors showed a 56% significant relative risk reduction in postoperative pancreatic fistula. Up to now, SOM230 did not receive any authorization to use in prevention of postoperative fistula from either the *Food and Drug Administration* (FDA) in the United States or the *European Medicines Agency—Agence Européenne des Médicaments* in the European Union. In view of this result, we can hypothesize that improved pharmacodynamics and higher affinity for somatostatin receptor lead to stronger pancreatic exocrine secretion inhibition, and better PF prevention.

Consequently, continuous intravenous infusion of somatostatin-14, the natural peptide hormone, associated with 10–50 times stronger affinity with all somatostatin receptors, should be associated with a decreased pancreatic fistula rate. Up to now, this hypothesis has been poorly tested in non-randomized or underpowered studies against placebo (35), nevertheless with encouraging results. Somatostatin-14, a safe and easy-to-use drug, is actually available in Europe, with an AMM, at 6 mg per day, in the treatment of postoperative pancreatic fistula. If somatostatin-14 showed a significant protective effect compared with octreotide, this would lead to an important improvement in patient care after pancreatic surgery. Natural somatostatin [also known as GHIH (growth hormone-inhibiting hormone) or SRIF (somatotropin release-inhibiting factor)] and other somatostatin analogs (SRIFa), such as octreotide or pasireotide, exert their pharmacological activity via binding to somatostatin receptors (sst). There are five known somatostatin receptors: sst 1, 2, 3, 4, and 5. Somatostatin receptors are expressed in different issues under normal physiological conditions. Somatostatin and its analogs activate these receptors with different potencies, and this activation results in a reduced cellular activity and inhibition of endocrine and exocrine secretion (36). Somatostatin is a 14-amino-acid peptide hormone that suppresses secretions from the exocrine pancreas among its several effects (37, 38). Compared with octreotide acetate (commercially available as Sandostatine), somatostatin exhibits a binding affinity, which is 300–500 times higher for human sst1 and sst4, 10–20 times higher for human sst3 and 5, and 2 times higher for human sst2. Compared with SOM230, somatostatin exhibits a binding affinity also always superior for all sst receptors. In view of these data, using continuous intravenous infusion of somatostatin would allow a stronger inhibition of pancreatic exocrine insufficiency and consequently a stronger prophylactic effect on pancreatic fistula. The 6 mg somatostatin posology is clinically and routinely used for the treatment of pancreatic fistula, with a very good tolerance. This is up to know the only posology with a proven clinical effect. Consequently, we decided to use the same posology to assess its preventive effect on clinically relevant pancreatic fistula.

## Ethics and Dissemination

The subject will be granted a reflection period between the delivery of the information and the signature of the consent form. The investigator or a physician representing the investigator is in charge to collect the consent form before the inclusion in the study protocol. The information sheet and a copy of the consent form, signed and dated by the research subject and by the investigator or the doctor representing the investigator, are given to the individual before his or her participation in the research. Moreover, the investigator will specify in the research participant's medical file the methods used for obtaining his or her consent as well as the methods used for providing information with the goal of obtaining their consent. The investigator will keep the original signed and dated copy of the subject's consent form. Subjects are prohibited from participating in another research or an exclusion period anticipated after the research defined by 90-day period after randomization. Subjects will not receive any compensation for participation in the study. In addition, subjects who are included in the study protocol will not be charged with any additional costs.

